#### Analysis of the chemical salivary properties of the saliva

##### Method for measurement of the buffer capacity

In this test, a 1 ml sample of saliva will be transferred to a sterile Falcon-type tube. Next, 3 ml of hydrochloric acid (0.005 N) will be added to this sample. The tube will be lightly shaken and allowed to rest for 10 min. Immediately thereafter, the pH will be measured with the aid of a pHmeter (DM-22 model; Digicrom Analítica Ltda., São Paulo, Brazil). Reference values are described in the study by Gomes et al. [38].

##### Method for measurement of cortisol levels

Cortisol will be the physiological biomarker used to assess the susceptibility to psychological and/or physical stress in the saliva samples. The changes in cortisol levels usually follow the circadian rhythm, which includes three phases. The first phase is the response to the cortisol awakening (RCA). This phase is defined as a high increase in cortisol levels within 30 min after awakening, followed by a high decline within the following 3 h. The second phase shows a gradual decline in cortisol during the rest of the day, reaching the lowest concentration during the first half of sleep. Finally, the third phase corresponds to a gradual increase in cortisol levels until awakening [41, 42].

Therefore, considering that cortisol secretion is regulated by the circadian cycle and that the salivary cortisol concentration is directly related to the degree of activation of the hypothalamic–pituitary–adrenal (HPA) axis [43], the authors hypothesize the existence of variability in cortisol levels in the saliva of patients with DS. Therefore, the cortisol levels (susceptibility to stress) will be assessed in two different periods, in the morning and at night. Reference values for salivary cortisol levels in the morning and at night are respectively < 0.78 μg/dl and < 0.20 μg/dl, in accordance with the recommendations of Castro and Moreira [43].

The level of salivary cortisol will be dosed by means of an enzyme immunoassay kit (product #1-1102; Salimetrics, State College, PA, USA) used at room temperature (25 °C). The sample volumes will be 25 μl with an incubation time of 60 min. The controls and the standards will be dosed in the same plate. The procedure follows the basic principle of the enzyme immunoassay, wherein competition occurs between an unlabeled antigen and an antigen labeled with enzyme by a determined number of binding sites on the antibody. The test set will be carried out on the microtiter plate which is coated by monoclonal antibodies to cortisol. The standard and unknown cortisol compete with the wild-rabbit peroxidase-linked cortisol. The wild-type rabbit isolated enzyme acts as an antigen by the antibody binding sites. After incubation, deactivated components will be removed by washing. Peroxidase-linked cortisol will be measured by the peroxidase enzyme reaction on the tetramethylbenzidine (TMB) substrate. This reaction will produce a blue color. A yellow color will be formed after the reaction is finished, with the addition of sulfuric acid. Optical density analysis will be performed by the absorbance reading of the solution at 450 nm (correction filter from 490 to 630 nm) (EON, Biotek Instruments, Inc., Winooski, VT, USA). The amount of peroxidase cortisol, which will be detected by means of color intensity, is inversely proportional to the amount of present cortisol.

#### Analysis of the microbiological properties of the saliva

##### Method for measurement of *Pseudomonas aeruginosa* species

The methodology for the isolation and identification of *P. aeruginosa* will be performed to evaluate the risk of occurrence of aspiration pneumonia. No cleaning of the tongue must be accomplished by the patients with DS for at least 24 h. The mouthwash samples, which will be collected in physiological solution, will be centrifuged, resuspended, and seeded, in duplicate, in Petri dishes containing MacConkey agar (Difco, Detroit, MI, USA) for the isolation of enterobacteria/pseudomonas. The plates will be incubated at 37 °C for 48 h. Thereafter, the number of colony-forming units per milliliter (CFU/ml) will be calculated. Colonies with different morphologies will be stained by the Gram method. Five colonies of Gram-negative bacteria will be isolated in agarose gel and incubated at 37 °C for 24 h. Then, the tubes will be stored at 4 °C. The enterobacterial/pseudomonas strains will be identified by the API20 E system (Bio-Merieux, France), aiming at the detection of *P. aeruginosa* species. This methodology is described in the study by Pereira et al. [44].

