**Methods:**

The patients with DS will be randomly selected and divided into three groups (DS-NMES, DS-MA, and DS-OA_m_) with a minimum of 10 patients in each group. A thermosensitive microchip will be embedded in the OA_m_ to record its compliance. The therapeutic effects on masticatory muscle function will be investigated through electromyography, a caliper, and a force-transducer device; the sleep variables, in turn, will be evaluated by means of polysomnography. The physicochemical and microbiological properties of the saliva will also be analyzed, including the salivary flow, viscosity, buffer capacity, cortisol levels (susceptibility to psychological and/or physical stress), and *Pseudomonas aeruginosa* levels (risk of aspiration pneumonia) in these patients. The methods determined for this study will be carried out prior to and after 2 months of the recommended therapies.

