**Discussion:**

The primary outcomes would be the improvement and/or reestablishment of the function of masticatory muscles and the physiological sleep variables in this target public since individuals with DS commonly present generalized muscular hypotonia and dysfunction of the oropharyngeal musculature. As a secondary outcome indicator, the impact of the applied therapies (NMES, MA, and OA_m_) on the salivary microbiological and physicochemical properties in DS individuals will also be assessed. Furthermore, the compliance of OA_m_ usage will be measured through a thermosensitive microchip.

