### Aims and hypotheses

This study aims to assess the physiologic sleep variables, masticatory functions of the bilateral masseter and anterior temporalis muscles, and salivary parameters by means of PSG, sEMG, and specific salivary tests (levels of cortisol, presence of *Pseudomonas aeruginosa*, salivary flow, and pH) respectively, prior to and after neuromuscular electrical stimulation (NMES), the mastication apparatus (MA), and the mandibular advancement oral appliance (OA_m_) in patients with DS. It is hypothesized that oxyhemoglobin desaturation, caused by sleep apnea events, can lead to harmful functions of the neuromuscular system in patients with DS, reducing muscle tonus, which in turn may facilitate obstruction of the upper airways. Moreover, sleep breathing disorders may also lead to sleep architecture fragmentation and increase the arousal index, causing fatigue, nonrestorative sleep, excessive daytime sleepiness, learning and memory difficulties, which may result in low performance in daily tasks, and alterations in the physiological patterns of the various systems of the organism, creating a scenario for the emergence of several comorbidities, including cardiovascular disease that is very common in these individuals. Looking at these problems, it is expected that the OA_m_ will promote a dimensional increase in the oral pharynx during sleep, favoring the airflow and allowing the elimination and/or reduction of snoring and of obstructive sleep apnea. The electrical activity of the masticatory muscles may also be modulated, contributing to reduce the nocturnal obstruction. Furthermore, it is expected that NMES and the MA will contribute to the balance of masticatory muscular functions by means of recruiting muscle fibers. This muscular recruitment will reduce hypotonia and adjust the functions to the physiologic patterns of electrical muscle activity, both in rest and in isometric positions [31, 32]. The samples will be divided according to the randomization rules into three groups: neuromuscular electrical stimulation (NMES), which will be applied to the individuals in Group 1 (DS-NMES); mastication apparatus (MA), which will be applied to individuals in Group 2 (DS-MA); and mandibular advancement oral appliance (OA_m_), which will be applied in individuals in Group 3 (DS-OA_m_). All clinical interventions will be carried out during a period of 2 months.

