#### Protocol for salivary parameters

##### Saliva sample collection

Five steps will be defined in order to analyze the physical (determinations of the salivary flow and viscosity), chemical (buffer capacity and cortisol levels), and microbiological (levels of *P. aeruginosa*) properties of the saliva. In the first step, the patient must ingest no drink or foods for 2 h before saliva collection. The second step is rinsing the mouth thoroughly with distilled or deionized water (20 ml) for 20 s and collecting saliva samples 30–40 min after rinsing. The third step is to analyze the physical properties; a gustatory sialagogue will be applied as drops on the back of the tongue for 5 min, at an interval of 4 drops/min, to stimulate the saliva in patients with muscular hypotonicity and cognitive deficit. In order to analyze the chemical properties, the digital mechanical stimulation or milking of the major salivary glands will be carried out for 5–10 min. In the fourth step, simultaneously, the salivary flow will be aspirated by means of a low-power suction device (Aspiramax MA 520; NS, São Paulo, Brazil) and placed in a graduated sterile test tube which will be refrigerated at a temperature of 4 °C. In the fifth step, the saliva samples will be stored in a container at a temperature of 4 °C and later transported to the genome laboratory. In order to ensure identification of the *P. aeruginosa* species, the saliva sample must be analyzed within a maximum period of 3 h.

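### *P. aeruginosa* is named as a level in some sections and as presence in others; the laboratory steps give a mixed Gram-negative count plus detection, with no stated step to a species level, and two different specimens are described

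*Protocol article*

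**What the plan says.** **Role.** The abstract's Discussion paragraph makes the salivary results secondary: "As a secondary outcome indicator, the impact of the applied therapies (NMES, MA, and OA_m_) on the salivary microbiological and physicochemical properties".

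**What is to be measured.** The abstract's Methods paragraph names *P. aeruginosa* "levels (risk of aspiration pneumonia) in these patients". Saliva sample collection opens with "Five steps will be defined in order to analyze the physical (determinations of the salivary flow and viscosity), chemical (buffer capacity and cortisol levels), and" and goes on to give levels of the species as the microbiological property. Aims and hypotheses instead lists "specific salivary tests (levels of cortisol, presence of" the species, and the main Discussion section repeats that wording.

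**How it is to be measured.** The method section for *P. aeruginosa* plates the sample in duplicate on MacConkey agar, to isolate enterobacteria and pseudomonas. After 48 h, "Thereafter, the number of colony-forming units per milliliter (CFU/ml) will be calculated". Gram staining of the differing morphologies follows, and then "Five colonies of Gram-negative bacteria will be isolated in agarose gel and incubated at 37 °C for 24 h". Strains are identified by API20 E with the aim of detecting the species. The section refers the method to a cited study.

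**Specimen.** Saliva sample collection describes aspirated saliva and, for this species, requires that "the saliva sample must be analyzed within a maximum period of 3 h". The method section says "The mouthwash samples, which will be collected in physiological solution, will be centrifuged, resuspended, and seeded".

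**The concern.** A level of one species needs a count of that species. The only count described is taken before any colony has been identified, on a medium that the protocol itself says it uses for a wider group. A change in that number over 2 months, or a difference between arms, could come from any organism in the group. Yet the abstract links the outcome to aspiration pneumonia risk from *P. aeruginosa* specifically.

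If presence is the intended outcome, the question becomes how reliably the identification step finds the species when it is only part of the growth. The choice also affects the analysis. The tests named under Statistical analysis (paired *t*, Wilcoxon, ANOVA, Mann–Whitney) suit a count, not a paired yes/no result.

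The specimen matters in either case. A concentration in a resuspended pellet depends on the rinse and resuspension volumes and is not a concentration in saliva.

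**Working it through.** The protocol states no carriage rate, detection rate or sample size for this outcome, so there is no figure of its own to reproduce.

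**1. Does any stated step give a species level?** The order in the method section is:
- seed on MacConkey agar in duplicate;
- incubate for 48 h;
- calculate CFU/ml;
- Gram-stain the differing morphologies;
- isolate five Gram-negative colonies;
- identify by API20 E.

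No count per morphology is stated, nor is there a rule that scales the total by the identified share. The outputs are therefore (a) CFU/ml of the mixed group and (b) whether *P. aeruginosa* was detected.

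**2. How sensitive is detection?** Inputs:
- n = 5 colonies, from the method section, which does not say whether this is per sample, per plate or per morphology;
- s = the share of *P. aeruginosa* among Gram-negative colonies, which the documents do not give, so a range is assumed;
- random picking, also an assumption.

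Probability of missing the species with five picks per sample = (1 − s)^5:

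| Assumed s | Missed | Detected |
|---|---|---|
| 5% | 0.95^5 = 77% | 23% |
| 10% | 0.90^5 = 59% | 41% |
| 20% | 0.80^5 = 33% | 67% |
| 30% | 0.70^5 = 17% | 83% |
| 50% | 0.50^5 = 3% | 97% |

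For 95% detection, s must be at least 1 − 0.05^(1/5) = 45%.

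If five were taken from each of the two duplicate plates (ten picks), the miss probability would be (1 − s)^10. At 10% this is 0.59 × 0.59 = 35%, and at 20% it is 0.328 × 0.328 = 11%. The unit left unstated therefore changes the answer considerably.

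**3. Could a level be recovered as CFU/ml × k/5?** Here k is the number of the five colonies identified as *P. aeruginosa*. Under random picking the estimated share moves in steps of 1/5 = 20%. The exact (Clopper–Pearson) 95% intervals for the share are:
- 0/5: 0 to 52%
- 1/5: 0.5 to 72%
- 2/5: 5 to 85%
- 3/5: 15 to 95%

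If colonies are instead selected by morphology, detection may improve, but k/5 no longer estimates the share. A level then needs a separate count for each morphology.

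**4. Specimen.** In Saliva sample collection the mouth is rinsed with distilled or deionized water, and saliva is aspirated 30–40 min later. In the method section the cultured material is itself a rinse, in physiological solution, which is centrifuged and resuspended. Both passages concern identification of the same species, and they describe different materials.

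**The case against.** The strongest reply is that the outcome is presence. The aims and the main Discussion say so, and the method section ends on detection, which its steps can deliver. That stands. What remains is an inconsistency with the abstract and the saliva collection section, plus a CFU/ml figure whose purpose is not stated.

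A reader might infer that a *P. aeruginosa* level cannot be derived at all. The documents do not support that. Colonies are distinguished by morphology before identification, so a count per morphology, or a total scaled by the identified share, is compatible with the text. The cited method, which is not at hand, may contain such a rule. What can be said is that the protocol states none.

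A reader might also take the miss rates as predictions, or conclude that carriers will appear to clear the organism by chance at a known rate. That would need random picking, five colonies per sample and a known share. The first two are not stated and the third is not given. Selection by morphology could raise detection.

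Nor does the protocol say that the MacConkey total will be reported as *P. aeruginosa*. That is a risk created by the wording, not a stated intention.

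Finally, picking rules and volumes are bench details that an article may leave out, and with fixed volumes a before–after comparison of mouthwash counts would be valid. This is fair for the volumes. It does not resolve which specimen is cultured or which endpoint is meant, because the article states both in two conflicting ways.

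**Conclusion.** The point holds in this form. The protocol names one secondary outcome in two ways, level and presence. The described procedure gives a mixed Gram-negative count and a detection result, and no stated step turns them into a species level. Two sections also name different specimens for the same test. These conclusions rest on the text alone and need no assumption.

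The possible loss of sensitivity is conditional: 59% missed at an assumed 10% share and 33% at 20%, with five random picks per sample, and less if more colonies are taken or if selection by morphology works well. Neither the primary outcomes nor the sample size, which is based on EMG activity, is affected. It is worth correcting before samples are processed, because unrecorded morphotype counts cannot be recovered once the plates are gone.

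**What to change.** - Choose one endpoint, level or presence, and use it in the abstract, the aims, the saliva sections and the Discussion.
- Record CFU/ml separately for each colony morphotype on the duplicate plates.
- Put at least one colony of every Gram-negative morphotype through the API20 E identification already planned. Report *P. aeruginosa* CFU/ml, or presence, from the morphotypes so identified. If a fixed number of colonies is kept, state whether it applies per sample, per plate or per morphotype.
- Label the MacConkey total as mixed enterobacteria/pseudomonas growth.
- Name one specimen in both Saliva sample collection and the *P. aeruginosa* method section, with the same rinse and resuspension volumes at both assessments.

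The cost is protocol wording and a few extra identification strips per sample. No extra visit or patient procedure is needed.

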#### Protocol for neuromuscular electrical stimulation

Neuromuscular electrical stimulation (NMES) will be used to improve and/or balance the muscular tonus and to modulate masticatory and oropharyngeal muscle functions. This method has proven to be a safe and effective therapy [15]. The Neurodyn Imbramed II equipment with a four-channel device will be used (Fig. 7). NMES is a noninvasive, safe, and effective treatment, which uses electrical impulses to stimulate and/or modulate a group of injured and/or altered muscle functions. It can also favor blood circulation, improve muscle spasms, reduce edema caused by inflammatory processes, and increase muscle strength, resulting in gain of the muscular tonus [20, 21]. The equipment will deliver a low-current intensity in order to induce action potentials in motor nerves, resulting in the activation of motor units [45, 46]. This therapy produces electrical stimulation on a group of muscles, through surface electrodes correctly placed on the muscles. NMES will be performed according to Guidelines 601 and 601-2-10 of the International Electrotechnical Commission, which establishes the rules for the respective usage of electromedical devices and electrical stimulators. The surface electrodes will be placed on the muscle motor point (bilateral masseter and anterior temporalis). The following parameters will be used: pulse frequency of 50 Hz, pulse width of 250 μs, on/off ratio of 5 s of stimulation and 10 s of rest for 20 min, and low-current intensity (range from 12 to 19 mA) per session, depending on patient sensitivity, and according to the protocol developed by Giannasi et al. [14, 15]. The patients will undertake three 20-min sessions per week of NMES on the bilateral masseter and the anterior temporalis muscles during a 2-month period. The described parameters may evoke muscle response with minimal discomfort to the patients, although most patients usually do not mention feeling any discomfort or pain. A visible muscle contraction will be noted when NMES is applied, meaning that the electrical stimulus produced the necessary contraction.

**Fig. 7 Fig7:**
[figure not shown]
Four-channel neuromuscular electrical stimulation (Neurodyn II Ibramed) equipment

#### Protocol for mastication apparatus

The mastication apparatus (MA) will be used to strengthen, stimulate, and modulate the masticatory muscles, showing a safe, good cost–benefit, and effective myofunctional approach [13, 47]. This MA is composed of two mastication instruments, Hiperboloide® (M.C. CHEIDA—ME, São Paulo, Brazil; http://www.hiperboloide.com), which are fixed in a support rod (SR). This SR is formed from a body of compact or fenestrated thermoplastic material and a stainless-steel wire with two free distal tips to couple the hyperboloids (active tips) (Fig. 8), which was developed by the transdisciplinary team of the CEBAPE-UNESP (the patent process is in progress, under protocol number 18CI038). Mastication apparatus therapy will be performed for 5 min, six times per day, with a minimum interval of 2 h between sessions, and for a period of 2 months. The individuals will simultaneously bite into the two active tips of the MA for 3 s and will release it for 1 s for a total duration of 5 min. This protocol was developed by Giannasi et al. [13]. These patients will be instructed to bite the MA in a slow rhythm. The therapy must be interrupted if the patient complains about feeling pain. After the mechanical exercises, the patients and/or caregivers will be instructed to clean the support rod with running water to remove residual remnants, dry it, and then store it in a safe, fresh, and clean location.

**Fig. 8 Fig8:**
[figure not shown]
Hyperboloid® fixed to the support rod

#### Protocol for the mandibular advancement oral appliance

The mandibular advancement oral appliance (OA_m_) is one of the most commonly used therapies to treat OSA safely and effectively. It is comfortable, silent, portable, and well tolerated. The appliance will protrude the mandible and base tongue, leading to an increase in upper airway dimensions. All of this alteration allowed by mandibular protrusion will promote the reduction/elimination of snoring and other respiratory events, as well as associated symptoms [48]. OA_m_ fabrication will be based on the definition of an effective device to treat OSA published by the American Academy of Dental Sleep Medicine. The OA_m_ features areas are follow - custom fabricated, allow titration (gradual mandibular advancement) and lateral movement, occlusal coverage, easy and suitable placement and removal by the patient or caregiver, and retentive relationship with the teeth [37]. The patients will use the oral appliance only during sleep, for a 2-month period. The OA_m_ titration will be done with increments of 0.25–1.0 mm, weekly or biweekly. The appliance will be constructed with acrylic resin in two parts (one for the upper arch and one for the lower arch), with complete coverage of the occlusal sides of the teeth, joined together by a hyrax 13-mm expansion screw on each side. The OA_m_ will be fitted and instructions on how to use the device will be given. The titration will be performed based on the needs of each individual, with mandibular advancement of 0.25-mm increments per turn [49]. The amount of advancement will be done based on reports by the patient and their caregivers regarding reduction in snoring, sleep apnea events, and initial symptoms and/or based on patients’ physiological limitations according to the advancement protocol developed by Giannasi et al. [49]. Not always is a great amount of protrusion necessary [50].

Patients will use the OA_m_ with an embedded temperature-sensitive microsensor with on-chip readout integrated electronics TheraMon® (Fig. 9). The data recorded in the chip will be read through a dedicated reading station. This microsensor will allow the measurement of objective OA_m_ compliance, based on the assumption that the oral appliance was worn when a temperature > 35 °C was recorded. The objective measurement is expressed as the objective mean rate of OA_m_ usage in number of hours used per day, and as the percentage of days of OA_m_ usage per week [39, 40]. The patient will be considered compliant when OA_m_ usage > 4 h per night. This information allows for calculation of the Mean Disease Alleviation (MDA), as a measure of therapeutic effectiveness [51–53]. The MAD, expressed as a percentage, is calculated as: MAD = [(adjusted objective × therapeutic efficacy) / 100].

